## Abstract

**Background:**

Secondary hyperparathyroidism is a common feature in patients with chronic kidney disease. Its serious clinical consequences include renal osteodystrophy, calcific uremic arteriolopathy, and vascular calcifications that increase morbidity and mortality.

Reduced synthesis of active vitamin D contributes to secondary hyperparathyroidism. Therefore, this condition is managed with activated vitamin D. However, hypercalcemia and hyperphosphatemia limit the use of activated vitamin D.

In Denmark alfacalcidol is the primary choice of vitamin D analog.

A new vitamin D analog, paricalcitol, may be less prone to induce hypercalcemia and hyperphosphatemia.

However, a randomised controlled clinical study comparing alfacalcidol and paricalcitol has never been performed.

The primary objective of this study is to compare alfacalcidol and paricalcitol. We evaluate the suppression of the secondary hyperparathyroidism and the tendency towards hyperphosphatemia and hypercalcemia.

**Methods/Design:**

This is an investigator-initiated cross-over study. Nine Danish haemodialysis units will recruit 117 patients with end stage renal failure on maintenance haemodialysis therapy.

Patients are randomised into two treatment arms. After a wash out period of 6 weeks they receive increasing doses of alfacalcidol or paricalcitol for a period of 16 weeks and after a further wash out period of 6 weeks they receive the contrary treatment (paricalcitol or alfacalcidol) for 16 weeks.

**Discussion:**

Hyperparathyroidism, hypercalcemia and hyperphosphatemia are associated with increased cardiovascular mortality in patients with chronic kidney disease.

If there is any difference in the ability of these two vitamin D analogs to decrease the secondary hyperparathyroidism without causing hypercalcemia and hyperphosphatemia, there may also be a difference in the risk of cardiovascular mortality depending on which vitamin D analog that are used. This has potential major importance for this group of patients.

**Trial registration:**

ClinicalTrials.gov NCT004695

## Background

Secondary hyperparathyroidism is a common complication of chronic kidney disease that is mainly caused by decreased synthesis of 1,25(OH)_2_vitamin D and phosphate retention due to reduced kidney mass, and the resultant hypocalcemia.

Treatment involves suppression of the parathyroid hormone (PTH) production by restoration of 1,25(OH)_2_vitamin D levels by replacement therapy [1]. However, 1,25(OH)_2_vitamin D stimulates intestinal phosphate and calcium absorption as well as phosphate and calcium mobilisation from bone, leading to an increased risk of hyperphosphatemia and hypercalcemia. Hyperphosphatemia and hypercalcemia are major risk factors for vascular calcification and coronary artery disease, the major cause of death in patients with chronic kidney failure [2-4]. Therefore, a vitamin D analog that suppresses the secondary hyperparathyroidism with low calcemic and phosphatemic activity would be of interest.

The two vitamin D analogs available in Denmark are alfacalcidol (1α(OH)D_3_) and paricalcitol (19-norD_2_). Their efficacy in suppressing hyperparathyroidism without causing hyperphosphatemia and hypercalcemia has never been compared.

A randomised, controlled study comparing paricalcitol and calcitriol found that paricalcitol could control hyperparathyroidism with fewer sustained episodes of hypercalcemia and increased calcium × phosphate product than calcitriol (1,25(OH)_2_D_3_) [5,6]. The lower calcemic and phosphatemic activities of paricalcitol can be attributed to decreased stimulation of bone resorption, and intestinal calcium and phosphate absorption [7,8].

Alfacalcidol is converted to calcitriol by the liver enzyme 25 hydroxylase [9]. If alfacalcidol only has effects when converted into calcitriol, we could apply the data from the existing studies, and expect alfacalcidol to be more calcemic and phosphatemic than paricalcitol.

However, a few studies intimate that alfacalcidol does not need to be hydroxylated into calcitriol before exerting its effects. Alfacalcidol apparently has its own intrinsic effects. With similar doses of alfacalcidol and calcitriol mediating the same degree of suppression of PTH, the peak concentration of 1,25(OH)_2_D_3 _is markedly lower after alfacalcidol administration than after calcitriol administration [10]. Also the suppression of PTH secretion from bovine thyroid glands in vivo, where the renal 25-hydroxylation of alfacalcidol is unavailable, is equal between alfacalcidol and paricalcitol [11].

Previous studies are not able to guide the clinician in choosing between alfacalcidol and paricalcitol when treating the patient with kidney disease and secondary hyperparathyroidism. Furthermore, paricalcitol is more expensive than alfacalcidol and needs greater justification if prescribed.

This is the first clinical study investigating whether there is a difference between the ability of alfacalcidol and paricalcitol to suppress secondary hyperparathyroidism in patients receiving chronic haemodialysis therapy without causing hyperphosphatemia and hypercalcemia. This study has been requested several times both in the literature and in the everyday clinical practice [12]. To address this problem, we are currently recruiting for this non-commercial investigator-initiated study.

## Methods/design

### Participants

Eligible subjects are > 18 years old and receiving chronic haemodialysis therapy for at least 3 month prior to screening in any of nine Danish haemodialysis outpatient clinics. After a period of minimum 6 weeks wash out, without any kind of vitamin D supplement, and sufficiently regulated p-phosphate (<1.8 mmol/l) and ionised p-calcium (<1.25 mmol/l), the patients are candidates for inclusion if p-iPTH is >350 pg/ml (37,1 pmol/l). The maximal allowed dose of calcium-containing phosphate-binders is 1600 mg elementary calcium a day at the time of inclusion. The patients may not be scheduled for parathyroidectomy or planned to start treatment with calcimimetics according to the local guidelines in the participating departments. Anticonception and negative pregnancy test should be present for fertile women. They are not admitted to the study if any of the following criteria are present (1) malignancy during the past five years (2) expected survival less than one year (3) pregnancy or breast feeding (4) allergy to any ingredient of Etalpha^® ^or Zemplar^® ^(5) in treatment with calcimimetics (6) participating in any other clinical trials which could affect the endpoints.

### Interventions

The study design is a crossover design where the patients are randomised into two treatment arms (Figure 1). The randomisation is performed after 6 weeks wash out during which the patients are not allowed to receive any kind of vitamin D supplement. The first arm receives alfacalcidol for 16 weeks and then goes through another 6 weeks wash out period before they receive paricalcitol for 16 weeks. The second arm receive paricalcitol for 16 weeks and then goes through another 6 weeks wash out period before they receive alfacalcidol for 16 weeks. The drugs are given at the end of haemodialysis treatment two or three times a week depending on the frequency of haemodialysis treatment. The start dose of alfacalcidol (Etalpha^®^Injection) is 3 μg a week and the start dose of paricalcitol (Zemplar^®^Injection) is 9 μg a week. Every second week the dose is titrated 50% according to p-phosphate, p-calcium and p-iPTH. As long as p-phosphate <1.8 mmol/l and ionised p-calcium <1.30 mmol/l and p-iPTH>150 pg/ml the dose is increased. When p- iPTH ≤ 150 pg/ml and p-phosphate <1.8 mmol/l and ionised p-calcium <1.35 mmol/l the dose is retained. If at any time p-phosphate >1.8 mmol/l or ionised p-calcium >1.35 mmol/l in two repeated measurements the dose is reduced.

**Figure 1 F1:**
[figure not shown]
**Flow chart for comparative cross-over study of alfacalcidol and paricalcitol**. After a 6 week wash out period, 117 patients are included. Every participating patient receives 16 weeks of treatment with alfacalcidol and 16 weeks of treatment with paricalcitol. The order of the treatments is decided by randomisation.

After inclusion the dose of calcium-containing phosphate-binders can only be unchanged or reduced. Elevated p-phosphate should be treated thoroughly with calcium-free phosphate-binders, dietary intervention and re-evaluation of the dialysis dose. Elevated p-calcium should lead to dietary intervention and reduction of calcium containing phosphate binders. The calcium concentration of dialysate is fixed to 1.25 mmol/l.

### Objectives

In the current study we test the hypothesis, that there is a difference between the ability of alfacalcidol and paricalcitol to suppress secondary hyperparathyroidism in patients receiving chronic haemodialysis without causing hyperphosphatemia and hypercalcemia.

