### Outcomes

The primary efficacy end point is the proportion of patients achieving ≥ 30% reduction in iPTH from baseline until the last 4 weeks of treatment with alfacalcidol or paricalcitol. The secondary outcomes is changes in ionised p-calcium, p-phosphate, calcium × phosphate product, p-alkaline phosphatase, p-25(OH)vitamin D, p-1,25(OH)_2_vitamin D, blood pressure, pulse and pulse pressure from baseline until the end of treatment with alfacalcidol or paricalcitol respectively. The frequency of parathyroidectomy or need for calcimimetics is registered.

Safety endpoints are b-haemoglobin, b-leukocytes, b-trombocytes, p-sodium, p-potassium, p-magnesium, p-bicarbonate, p-creatinine, p-urea, urea reduction rate, p-albumin, p-alanine aminotransferase, p-bilirubin, p-C-reactive protein and weight measured at the beginning and after each treatment period.

All laboratory samples are drawn from the blood lines of the dialyzer before start of the dialysis. P-iPTH, ionised p-calcium and p-phosphate are measured every second week during the treatment periods, the others parameters are measured at the beginning and the end of each treatment period. The urea reduction rate is calculated from a urea measured before dialysis and a urea measured immediately after dialysis. All laboratory analyses are performed at the participating departments' local laboratories.

Blood pressure and pulse are measured after 5 minutes rest before dialysis, and weight is measured before the dialysis session with clothes but no shoes.

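### The trial asks about iPTH suppression without hypercalcaemia and hyperphosphataemia, but no named outcome counts either event, and start-to-end changes under shared titration limits measure them weakly.

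*Protocol article*

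**What the plan says.** The Objectives section frames the hypothesis as a difference in ability to "suppress secondary hyperparathyroidism in patients receiving chronic haemodialysis without causing hyperphosphatemia and hypercalcemia". The Abstract, straight after stating the primary objective, adds: "We evaluate the suppression of the secondary hyperparathyroidism and the tendency towards hyperphosphatemia and hypercalcemia". The end of the Discussion restates the aim as suppression at doses that do not raise calcium or phosphate.

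The Outcomes section defines efficacy thus: "The primary efficacy end point is the proportion of patients achieving ≥ 30% reduction in iPTH from baseline until the last 4 weeks of treatment". No calcium or phosphate condition is attached. Sample size and Statistical methods use this same iPTH response.

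For the other half of the question, "The secondary outcomes is changes in ionised p-calcium, p-phosphate, calcium × phosphate product" and several further variables are taken "from baseline until the end of treatment with alfacalcidol or paricalcitol respectively". Statistical methods compares these changes by paired tests. Neither calcium nor phosphate is in the list of safety endpoints. The same section says that "P-iPTH, ionised p-calcium and p-phosphate are measured every second week during the treatment periods".

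Under Interventions, both drugs follow one titration rule. The dose rises while phosphate is below 1.8 mmol/l, ionised calcium is below 1.30 mmol/l and iPTH is above 150 pg/ml. It falls on phosphate above 1.8 mmol/l or "ionised p-calcium >1.35 mmol/l in two repeated measurements the dose is reduced". The text after the Figure 1 legend adds that high phosphate is treated with calcium-free binders, diet and review of the dialysis dose, and high calcium with diet and less calcium-containing binder.

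**The concern.** The hypothesis names two adverse events, and no listed outcome counts them. A patient whose iPTH falls by 30% with repeated hypercalcaemia on the way scores the same as one who responds cleanly.

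The outcome that carries the other half of the question compares two time points. Between them, the protocol reacts to each excursion by changing the dose, binders, diet or dialysis, on the same limits for both drugs. Part of the drug difference is thus spent on corrections before the final sample is drawn. The two-weekly series in which excursions would show has no named outcome built on it. The article's own Background summarises the earlier randomised comparison of paricalcitol with calcitriol in terms of sustained episodes, which is the kind of measure missing here.

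At stake is the sensitivity of the calcium and phosphate comparison. In an open-label trial there is a second risk: an episode definition chosen after values have accrued could be chosen to suit them.

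**Working it through.** **1. What the planned 117 covers.** Inputs from Sample size: 50% and 68% response, power 0.8, P = 0.05, McNemar; Statistical methods makes tests two-sided. Assume independent responses within a patient.

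- Difference d = 0.68 − 0.50 = 0.18. Discordant share ψ = 0.50 × 0.32 + 0.68 × 0.50 = 0.50.
- Miettinen: N = [1.96ψ + 0.8416√(ψ² − d²(3 + ψ)/4)]² / (ψd²) = [0.980 + 0.8416 × √0.22165]² / 0.0162 = 116.9, so 117.
- Connor: N = [1.96√ψ + 0.8416√(ψ − d²)]² / d² = 118.7, so 119; power at 117 is 0.794.

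The plan's figure reproduces, and it is for iPTH response alone.

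**2. Does titration attenuate the calcium change?** The article gives no calcaemic slopes or event rates, so only illustrations are possible. Both simulations below model calcium only and assume equal iPTH effect per unit of dose.

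*Illustration A:* eight two-weekly visits, 1.5-fold steps, calcium limits 1.30/1.35 mmol/l, one drug raising calcium twice as steeply. The end-of-period change differed 1.3 to 1.6 fold (0.04 to 0.05 mmol/l). Patients with any value above 1.35 were 32% against 9% in one scenario and 66% against 32% in another.

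*Illustration B:* mean baseline 1.15 mmol/l, eight visits, dose × 1.5 up and × 0.5 down on a single high value, slopes 0.02 and 0.03 mmol/l per dose unit.

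| | Slope 0.02 | Slope 0.03 |
|---|---|---|
| Calcium change, calcium limits applied | 0.158 | 0.156 |
| Calcium change, titrated on iPTH only | 0.268 | 0.402 |
| Ever above 1.35, limits applied | 58% | 80% |
| iPTH responders, limits applied | 94% | 83% |
| Responders never above 1.35 (share of all patients) | 41% | 19% |

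Attenuation is partial in A and almost complete in B. B reduces on one high value, whereas the protocol asks for two repeated measurements, so B overstates it. Both count single high values, not confirmed episodes. In B the iPTH response also separates (94% against 83%): the dose limit passes part of the calcaemic difference into the primary endpoint.

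**3. Could the planned change still detect A's gap?** Assume the SD of paired differences is 0.10 to 0.15 mmol/l (not in the article). Power ≈ Φ(δ√n/SD − 1.96).

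- n = 117, δ = 0.04: Φ(4.33 − 1.96) = 0.99 at SD 0.10; Φ(2.88 − 1.96) = 0.82 at SD 0.15.
- n = 117, δ = 0.05, SD 0.15: Φ(3.61 − 1.96) = 0.95.
- n = 90, δ = 0.04: about 0.96 at SD 0.10 and 0.71 at SD 0.15.

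So it often could.

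**4. Power of a joint responder at 117.** Multiply the planned iPTH rates by an assumed share of responders free of both events; independent pairs, Connor formula.

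| Free of events: alfacalcidol / paricalcitol | Joint rates | N for 0.8 power | Power at 117 |
|---|---|---|---|
| 80% / 80% | 40% v 54.4% | 191 | 0.59 |
| 60% / 60% | 30% v 40.8% | 310 | 0.40 |
| 60% / 80% | 30% v 54.4% | 66 | 0.97 |
| 80% / 60% | 40% v 40.8% | no usable contrast | – |

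The joint outcome could be weaker or stronger than the primary, or show nothing, which is why it fits a supportive role.

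**The case against.** The best defence is that the design already tests much of the joint question. Dose rises only within the calcium and phosphate limits, so the iPTH response is largely the suppression achievable inside them, which is the aim the Discussion states. A more calcaemic drug is held at a lower dose and can lose responders. This stands in part, and illustration B shows it. It does not close the gap: calcium-driven reduction waits for two repeated values, so a patient can have confirmed hypercalcaemia and still be counted a success.

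Second, an efficacy primary with separate calcium and phosphate secondaries is conventional, and how episodes are summarised is often left to a full protocol or analysis plan. That is fair as to detail. But the article does name a measure for these variables, the start-to-end change, and that measure fits the stated question poorly.

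Third, a composite has real weaknesses: it is unpowered, and its phosphate part also reflects binders, diet and dialysis. This stands. It is why separate episode outcomes should lead and the joint responder should only support them.

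A reader might go further and infer that shared titration forces end-of-period values to converge, so that the trial cannot answer its question. The documents do not support that. They give no slopes or event rates, illustration A leaves a gap the planned paired test would often detect, and near-complete convergence appears only under B's stricter reduction rule. Nor are the two-weekly values without any use: they drive titration, and Statistical methods promises to describe all data, including ranges.

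**Conclusion.** The point holds as a mismatch within the article. The question includes hypercalcaemia and hyperphosphataemia; the named outcomes count neither, and the change measure chosen for calcium and phosphate is attenuated by the shared limits and corrections. The primary endpoint compensates only in part.

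The size is not known. The simulated percentages rest on assumed calcium slopes and equal iPTH effect, leave phosphate out, and show direction only. The power of 0.71 to 0.99 for a 0.04 mmol/l gap rests on an assumed SD. The argument that phosphate behaves likewise comes from the titration and correction rules, not from a calculation. This is a worthwhile improvement to the secondary outcomes; it does not invalidate the primary comparison or the 117.

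**What to change.** Before outcome data are examined, prespecify from the two-weekly on-treatment values:

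- **Key secondary outcomes:** for each treatment period, the proportion of patients with at least one confirmed episode of ionised calcium above 1.35 mmol/l and, separately, of phosphate above 1.8 mmol/l, compared as paired binary data. Report the number of episodes per period as well. State what confirmation means, using the protocol's own notion of two repeated measurements.
- **Supportive outcome:** a joint responder, meaning at least 30% iPTH reduction in the last four weeks and no such episode in that period, analysed by the same paired method as the primary.
- **Context:** study-drug dose reached in each period.

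Keep the start-to-end changes as listed. Leave the primary endpoint, sample size and titration rule unchanged; the limits serve here only to define outcomes.

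Cost: protocol and analysis-plan wording and a few extra analyses, with no new visits, samples or patients. Downside: these outcomes are not separately powered, and the phosphate component partly reflects binder, diet and dialysis changes, so a null result on it should be read with caution.

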### Outcomes

The primary efficacy end point is the proportion of patients achieving ≥ 30% reduction in iPTH from baseline until the last 4 weeks of treatment with alfacalcidol or paricalcitol. The secondary outcomes is changes in ionised p-calcium, p-phosphate, calcium × phosphate product, p-alkaline phosphatase, p-25(OH)vitamin D, p-1,25(OH)_2_vitamin D, blood pressure, pulse and pulse pressure from baseline until the end of treatment with alfacalcidol or paricalcitol respectively. The frequency of parathyroidectomy or need for calcimimetics is registered.

Safety endpoints are b-haemoglobin, b-leukocytes, b-trombocytes, p-sodium, p-potassium, p-magnesium, p-bicarbonate, p-creatinine, p-urea, urea reduction rate, p-albumin, p-alanine aminotransferase, p-bilirubin, p-C-reactive protein and weight measured at the beginning and after each treatment period.

All laboratory samples are drawn from the blood lines of the dialyzer before start of the dialysis. P-iPTH, ionised p-calcium and p-phosphate are measured every second week during the treatment periods, the others parameters are measured at the beginning and the end of each treatment period. The urea reduction rate is calculated from a urea measured before dialysis and a urea measured immediately after dialysis. All laboratory analyses are performed at the participating departments' local laboratories.

Blood pressure and pulse are measured after 5 minutes rest before dialysis, and weight is measured before the dialysis session with clothes but no shoes.

### Sample size

We assume that the proportion of patients achieving ≥ 30% reduction in iPTH in the last four weeks of the treatment period would be 50% in the alfacalcidol group and 68% in the paricalcitol group [13,14]. Based on 0.8 power to detect a significant difference (P = 0.05, McNemars test), 117 patients is required for inclusion.

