### Statistical methods

The frequency of reaching a 30% reduction in iPTH for a minimum of 4 weeks is compared between the two treatments in the same person by McNemar test for paired observations. It is tested whether the effect is dependent of the order of the periods.

Furthermore the effect of the two treatments after the first period will be analysed separately from the second period.

The distribution of the variables and the changes in the variables from the start until the end will be described. Mean, median, standard deviation and range will be reported.

All tests are two-sided tests α = 0.05. The changes during the two treatments will be compared using tests for paired observations.

Parametric tests (paired t-test) will be used if the distributions are normal and non-parametric test (McNemar test and Wilcoxon signed ranks test) for ordered or continuous data.

All participants that are evaluable will be included in the statistical analysis.

The analysis will be performed in Statistica with the procedures: UNIVARIATA, FREQ and ANOVA.

The data analysis will be performed blinded. While doing the statistical analysis the treatment groups will be unknown.

All data will be described and the reason for missing values will be described. Every violation from the statistical plan will be described in the final publication.

All eligible subjects receives a written description of the study objective, schedule, benefits and risks, other treatment possibilities, funding and contact information.

They are offered a consultation providing further information. Here they can bring their relatives.

If the subject agrees to participate a written informed consent is signed.

The study is in compliance with the Helsinki Declaration and is approved by the Danish National Committee on Biomedical Research Ethics (SJ-27), the Danish Medicines Agency (EudraCT: 2006-005981-37) and Danish Data Protection Agency (2007-41-0503)

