## Discussion

This article describes the protocol of a randomised trial comparing the ability of alfacalcidol and paricalcitol to suppress secondary hyperparathyroidism without causing hypercalcemia and hyperphosphatemia in patients with chronic kidney disease. As far as we know, alfacalcidol and paricalcitol have never been compared in a randomised clinical trial before.

The advantage of the cross-over design is an elimination of the stochastic variation due to differences between individuals. This reduces the sample size needed. In Denmark in year 2007, there was 2037 haemodialysis patients and a death rate of 21.7% per year in this patient group [15]. Therefore, limiting the sample size is necessary.

When deciding the length of the treatment period it was a balance between different considerations. First, it should not be too long to avoid too many patients to drop out before completing the study. With a mortality rate of 21.7% a year, this is a problem [15]. Second, the treatment period should be long enough to reach a steady state in parathyroid hormone suppression. Going through other long term interventional studies with alfacalcidol or paricalcitol, 16 weeks seems to be the minimal feasible length [6,16]. Third, there is a risk of progression of the secondary hyperparathyroidism over time. However, secondary hyperparathyroidism is a chronic disease. The disease should not progress in a period of 44 weeks, as long as the patients are treated with some kind of active vitamin D.

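### The 117 patients to be included match the number of complete pairs that McNemar's test needs for 0.8 power, so the stated power has no visible margin for the drop-out the protocol itself expects

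*Protocol article*

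**What the plan says.** The Sample size section assumes that the share of patients with at least a 30% fall in iPTH "would be 50% in the alfacalcidol group and 68% in the paricalcitol group", and concludes: "Based on 0.8 power to detect a significant difference (P = 0.05, McNemars test), 117 patients is required for inclusion". Statistical methods adds "All tests are two-sided tests α = 0.05" and says that the responder frequency "is compared between the two treatments in the same person by McNemar test for paired observations". It limits the analysis to evaluable participants.

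The same 117 appears as the enrolment figure. The abstract says "Nine Danish haemodialysis units will recruit 117 patients with end stage renal failure on maintenance haemodialysis therapy", and the legend of Figure 1 says "After a 6 week wash out period, 117 patients are included".

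On follow-up, Interventions says "The first arm receives alfacalcidol for 16 weeks and then goes through another 6 weeks wash out period before they receive paricalcitol for 16 weeks"; patients in the other arm follow the same timetable in reverse order. On loss, the Discussion raises drop-out before completion when it justifies the length of the treatment period, and says "With a mortality rate of 21.7% a year, this is a problem". It uses the mortality figure to argue for short periods and a limited sample size. Nowhere does the article apply it to the number of patients.

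**The concern.** McNemar's test uses only patients with a classified response under both treatments. A patient who dies or leaves before the end of the second period contributes no pair. If 117 is the number of pairs needed, randomising 117 gives the planned power only when nobody is lost, and the protocol says it expects losses.

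At stake is how the design is described, not its validity: type I error and the treatment comparison are unaffected. The power figure tells readers how likely the trial was to detect an 18-point difference. If it is too favourable, a non-significant result may be taken as stronger evidence of no difference than the design supports. The Background says the dearer drug needs greater justification, so such a result would have practical weight.

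**Working it through.** **Inputs.** Responder shares 0.50 and 0.68, so d = 0.18; power 0.80; McNemar's test; N = 117 (Sample size). Two-sided alpha 0.05 (Statistical methods). Time from randomisation to the end of the second period: 16 + 6 + 16 = 38 weeks (Interventions; the first wash-out precedes randomisation). Mortality 21.7% a year (Discussion). The discordant share ψ is not given.

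**Step 1: reproduce 117.** Assume that the two responses in a patient are independent. Then ψ = 0.50 × 0.32 + 0.50 × 0.68 = 0.16 + 0.34 = 0.50. The Miettinen formula is

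n = [z_α ψ + z_β √(ψ² − d²(3 + ψ)/4)]² / (ψ d²)

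= [1.960 × 0.50 + 0.842 × √(0.25 − 0.0324 × 3.5/4)]² / (0.50 × 0.0324) = 116.9, that is, 117 pairs.

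The unconditional (Connor) formula, [z_α √ψ + z_β √(ψ − d²)]² / d², gives 118.7. Both results are numbers of complete pairs with nothing added for loss.

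**Step 2: apply the protocol's mortality to 38 weeks.** Survival is (1 − 0.217)^(38/52) = 0.836 if 21.7% is a yearly risk, or exp(−0.217 × 38/52) = 0.853 if it is a rate. Then 117 × 0.836 = 97.8 and 117 × 0.853 = 99.8, so about 98 to 100 pairs. At half that mortality (10.85% a year) survival is about 0.92, and about 108 pairs remain.

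**Step 3: power at those numbers.** Power = Φ{[d√n − z_α√ψ] / √(ψ − d²)}, with ψ = 0.50:

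| Complete pairs | Power |
|---|---|
| 117 | 0.794 |
| 108 (half mortality) | 0.76 |
| 100 | 0.728 |
| 98 | 0.719 |

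Exact enumeration of the uncorrected McNemar test agrees: 0.799 at 117 pairs and 0.725 at 98. With 98 pairs and ψ = 0.50, the difference detectable with 0.8 power is about 20 points instead of 18.

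**Step 4: sensitivity to within-patient correlation.** With correlation ρ, ψ = 0.50 − 2ρ√(0.50 × 0.50 × 0.68 × 0.32) = 0.50 − 0.466ρ.

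| ρ | ψ | Pairs | Power |
|---|---|---|---|
| 0.10 | 0.453 | 108 | 0.80 |
| 0.15 | 0.430 | 98 to 100 | 0.785 to 0.793 |
| 0.20 | 0.407 | 98 | 0.81 |

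Modest correlation therefore closes the gap.

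**The case against.** The strongest reply is that the shortfall depends on independence, which the article never states. The Discussion justifies the crossover by its removal of variation between individuals, so its authors expected a patient's two responses to be alike. Any positive correlation lowers the discordant share and raises power, and Step 4 shows that little is needed. This stands. A reader might infer that the trial is underpowered, or that the match at 116.9 proves the sponsor assumed no correlation. The document supports neither. Formula variants at the same discordance run from 114 to 125, and a calculation with ψ near 0.41 to 0.42 would need only 98 to 100 pairs, so 117 could hold an undisclosed allowance for loss. Nothing in the text says that it does.

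Second, 21.7% describes all Danish haemodialysis patients, whereas the trial excludes those expected to survive less than a year and those with recent malignancy. The full rate may therefore overstate deaths, which is why the half-rate case is shown. Losses other than death would work the other way, but the article gives no figure for them.

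Third, an exact McNemar test gives power of only 0.68 at 98 pairs, which looks worse. The same test gives 0.764 at the full 117, so much of that gap to 0.8 comes from changing the test. The article does not specify the exact version, and the point does not rest on it.

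Fourth, a condensed article may leave the discordance input to a fuller document. Its absence is not a fault in itself. It matters here because the power cannot be restated without it.

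**Conclusion.** The point holds in a limited form and should be fixed. On the article's own inputs, 117 serves both as the number of complete pairs that fits the stated power and as the number enrolled, while the expected drop-out is acknowledged but not carried into the number. If responses are independent, the planned power is about 0.72 to 0.73 at the cited mortality and about 0.76 at half of it. With a correlation of about 0.15 to 0.2 (at 98 to 100 pairs) or about 0.10 (at 108 pairs) it returns to about 0.8. So the documents do not show that realised power will fall below 0.8; they show that the 0.8 is unsupported as written. The result rests on the inferred discordant share of 0.50, deaths as the only loss, and 38 weeks of exposure.

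**What to change.** In the Sample size section:

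- State how many patients are randomised and how many complete pairs are expected, and keep the two apart in the abstract and the Figure 1 legend.
- Give the discordant share or correlation that the calculation actually used. The sponsor must supply it; the 0.50 here is a reconstruction and should not be written in as the sponsor's own assumption.
- Restate the power with 117 randomised after the anticipated loss: about 0.72 to 0.76 if responses are independent, together with the range for modest correlation.
- If exact McNemar figures are quoted, show them beside their value of 0.764 at 117 pairs.

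This costs wording only, and probably a less favourable power figure. It changes no endpoint, test or allocation. If the sponsor prefers to keep 117 complete pairs, enrolment would have to rise to about 138 to 140 (117/0.853 to 117/0.836) to cover deaths alone at the cited rate, which is a larger change than restating the power.
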